## Abstract

**Background:**

Increasing experience with minimally invasive surgery and the development of new instruments has resulted in a tendency toward reducing the number of abdominal skin incisions. Retrospective and randomized prospective studies could show the feasibility of single-incision surgery without any increased risk to the patient. However, large prospective multicenter observational datasets do not currently exist.

**Objective:**

This prospective multicenter observational quality study will provide a relevant dataset reflecting the feasibility and safety of single-incision surgery. This study focuses on external validity, clinical relevance, and the patients’ perspective. Accordingly, the single-incision multiport/single port laparoscopic abdominal surgery (SILAP) study will supplement the existing evidence, which does not currently allow evidence-based surgical decision making.

**Methods:**

The SILAP study is an international prospective multicenter observational quality study. Mortality, morbidity, complications during surgery, complications postoperatively, patient characteristics, and technical aspects will be monitored. We expect more than 100 surgical centers to participate with 5000 patients with abdominal single-incision surgery during the study period.

**Results:**

Funding was obtained in 2012. Enrollment began on January 01, 2013, and will be completed on December 31, 2018. As of January 2016, 2119 patients have been included, 106 German centers are registered, and 27 centers are very active (>5 patients per year).

**Conclusions:**

This prospective multicenter observational quality study will provide a relevant dataset reflecting the feasibility and safety of single-incision surgery. An international enlargement and recruitment of centers outside of Germany is meaningful.

**Trial Registration:**

German Clinical Trials Register: DRKS00004594; https://drks-neu.uniklinik-freiburg.de/drks_web/navigate.do?navigationId=trial.HTML&TRIAL_ID=DRKS00004594 (Archived by WebCite at http://www.webcitation.org/6jK6ZVyUs)

## Introduction

The surgical standard for many abdominal diseases is changing. Traditionally, operative treatments meant open resection with laparotomy. However, over the last two decades, laparoscopic surgery has become a valuable alternative to many procedures, for example, cholecystectomy, appendectomy, or colon resection [1-6].

Conventional laparoscopic surgery requires a number of ports and a specimen extraction incision. Increasing experience with minimally invasive surgery and the development of new instruments has resulted in a tendency toward reducing the number of skin incisions. Natural orifice transluminal endoscopic surgery (NOTES) is the closest we have come to scar-free surgery because it does not leave any visible scars on the surface of the body. But NOTES is still an experimental approach [7]. For that reason, single-incision laparoscopic surgery could represent an attractive approach to minimally invasive abdominal surgery [8]. Several recently published retrospective and randomized prospective studies could demonstrate that the single-incision single port/multiport technique is not associated with a higher rate of morbidity or mortality compared with conventional laparoscopic surgery [9-21]. The majority of the relevant literature documents single-incision cholecystectomy. Single-incision appendectomy, liver surgery, colon surgery, and gastric surgery have also been described [22-28].

The determination of differences in the safety of classic multitrocar techniques compared to the single-incision techniques in prospective randomized studies is still difficult because of the rarity of some relevant complications. For example, injury to the major bile duct during surgery, with a frequency of about 0.5%, is a rare but severe complication. Large prospective randomized studies with many thousands of subjects are necessary to answer some of these clinically relevant questions; however, such large prospective randomized studies are not necessarily feasible. Prospective multicenter observational quality studies should support the data of published prospective randomized studies on this subject.

While surgeons develop new techniques for entering the abdominal cavity, patient safety should remain important. This prospective multicenter observational quality study will provide a relevant dataset reflecting the feasibility and safety of single-incision surgery. This study focuses on external validity, clinical relevance, and the patient perspective. Accordingly, the single-incision multiport/single port laparoscopic abdominal surgery (SILAP) study will supplement the existing evidence, which is currently too sparse to allow evidence-based surgical decision making.

## Methods

### Trial Objectives

The aim of the trial is to collect data about indications, technical aspects, mortality, and morbidity of single-incision multiport or single port abdominal surgery in daily use. All types of single-incision multiport or single port abdominal surgery will be included in the study. Every participating center will receive a quality report every year (online in real time for the individual center and in a print version once a year for the complete study). The analysis time period for the annual quality report is one calendar year. This quality report will be available for each center by May of the ongoing year and will include data from the previous year.

### Trial Design

SILAP is a prospective nonrandomized multicenter observational quality study with no intervention.

### Trial Duration and Schedule

The duration of the trial for each patient is limited to the hospital stay. The trial duration itself is from January 2013 to December 2018 (see Figure 1). The actual overall duration or recruitment may vary.

**Figure 1 figure1:**
[figure not shown]
Trial duration.

### Study Population

All patients at the participating centers who are scheduled for single-incision multiport or single port abdominal surgery will be informed about the purpose of the observational trial. All types of abdominal surgery can be included. After being screened for the inclusion and exclusion criteria, eligible patients will be included in the trial (informed consent necessary) (see Figure 2). Surgery, examinations, and measures are not influenced by this observational trial.

**Figure 2 figure2:**
[figure not shown]
Trial flow chart.

### Number of Subjects and Trial Centers

A sample size calculation is not relevant for this observational quality study. A minimum of 100 surgical centers is expected. The participating centers will include a maximum of their patients fulfilling the inclusion criteria and not meeting an exclusion criterion. The data are documented using an Internet database including a self-plausibility control function.

### Inclusion Criteria

Subjects meeting all of the following criteria will be considered for admission to the trial: (1) patients (≥18 years) scheduled for elective or emergency single-incision multiport or single port abdominal surgery (all types of abdominal surgery), (2) ability of subject to understand character of the clinical trial, and (3) able and willing to provide written informed consent.

### Exclusion Criteria

Subjects presenting with the following criteria will not be included in the trial: participation in another intervention trial that interferes with the intervention and outcome of this study.

### Outcome Variables

The following endpoints will be used to answer the trial goals: (1) Mortality (hospital mortality), (2) Morbidity, which includes complications during surgery (eg, bleeding during surgery or injury of small or large bowel, common bile duct, urine bladder, ureter, solid organs, or other intraabdominal structures) and post-operative complications (eg, wound infection according to Centers for Disease Control and Prevention [CDC] criteria, intraabdominal infections, urinary tract infection, pneumonia, cardiac complications, pulmonary complications, intraabdominal bleeding after surgery, ileus, insufficiency of an anastomosis, reoperation, burst abdomen, or other complications), (3) Patient characteristics (sex, age, height in cm, weight in kg, duration of hospital stay, duration of hospital stay after surgery, routine or emergency surgery, date of surgery, American Society of Anesthesiologists classification [29], indication only for cholecystectomy), and (4) Technical aspects, such as type of surgery (ie, appendectomy or cholecystectomy), type of single-incision procedure (multiport or single port), location of the single incision (umbilical or other position), used port device or size and number of the trocars for single-incision surgery, success rate of the single-incision procedure (procedure finished in single-incision technique), incision to closure time (operation time), conversion rate, device for closing the cystic duct, use of holding sutures or other holding devices, and type of sutures for closing the fascia incision.

The assessment of outcome variables comprises (1) mortality, that is, death due to any cause at any time during the hospital stay, and (2) morbidity (during the hospital stay), including:

surgical site infections (SSIs) will be assessed at discharge and divided into superficial and deep incisional SSIs according to the CDC definition [30] (see Figure 3)post-op pulmonary infection (pneumonia) will be assessed at discharge and is defined as infection of the lung with either evidence of increased infection parameters (C-reactive protein/CRP >2mg/dl and/or leukocytes >10 0000/ml), which are not caused by a different pathologic process, or evidence of pulmonary infiltration in the chest x-ray, requiring antibiotic therapylesion of small or large bowel (any unplanned complete lesion of bowel)bleeding during surgery (any bleeding during surgery that required conversion to an open approach or to an multiple trocar approach or required transfusion)intraabdominal bleeding after surgery (requiring transfusion or surgery)intraabdominal infections (any kind of peritonitis, intraperitoneal abscess, infected bilioma requiring medication, drainage, or surgery)ileus (any kind of postoperative intestine passage disturbance requiring medication or surgery)insufficiency of an anastomosis (every anastomotic leak clinical or radiographic proven)burst abdomen (postoperative dehiscence of the fascia/peritoneum with or without dehiscence of the skin)

Other aspects for assessment are operation time (from skin incision to closure of wound), conversion rate (conversion from single incision to an open approach), and need for additional trocars.

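### The aim covers indications for all single-incision procedures, but the indication is recorded only for cholecystectomy

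*Protocol article*

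**What the plan says.** Trial Objectives gives the aim in one sentence: "The aim of the trial is to collect data about indications, technical aspects, mortality, and morbidity". The next sentence sets the scope: "All types of single-incision multiport or single port abdominal surgery will be included in the study". Study Population and Inclusion Criteria repeat that scope, and the latter admits both elective and emergency cases.

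Outcome Variables opens by tying its list to the aim: "The following endpoints will be used to answer the trial goals". Under patient characteristics the list gives sex, age, height, weight, lengths of stay, routine or emergency status, date of surgery and ASA class, and ends with "indication only for cholecystectomy". Under technical aspects it gives "type of surgery (ie, appendectomy or cholecystectomy").

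Statistical Procedures plans subgroup analyses by patient characteristics and technical aspects, with type of surgery as an example, and exploratory logistic regressions of prognostic factors on the outcomes.

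**The concern.** The aim and the variable list disagree. The aim promises data on indications for all procedures, while the list that is meant to serve the aim collects them for one. A study run exactly as written would reach its end without data on part of what it set out to describe.

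There is also a cost to interpretation. In a study without a comparison arm, complication and mortality figures are read against the kind of patient operated on. If the reason for surgery is unknown within a procedure group, patients operated on for quite different diseases are pooled. Resections for benign and for malignant colon disease are one example. A difference between subgroups, or between this study and the published evidence that the Conclusion proposes to compare it with, could then reflect the mix of diagnoses, and the data could not show whether it did.

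**Working it through.** The article states no figure on this point, so the check sets the aim beside the variable list.

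**Elements of the aim against the variables listed**

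| Element of the aim | Cholecystectomy | All other procedures |
|---|---|---|
| Indications | recorded | not recorded |
| Technical aspects | recorded | recorded |
| Mortality | recorded | recorded |
| Morbidity | recorded | recorded |

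Three of the four elements are covered for every procedure. One is covered for a single procedure.

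**Is this only condensed detail?** An article may leave detail to the full protocol, and silence about indications elsewhere would be no finding. Here the text states a restriction through the word *only*. The complication and technical lists are opened by *eg* or *such as*; the patient-characteristics list is not. A fuller document that collected indications for other procedures would contradict this sentence.

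**Can other variables stand in?**
- Type of surgery records what was done. For appendectomy it comes close to the reason, though it does not separate simple from perforated disease. For colon, liver and gastric surgery, all named in the Introduction as single-incision applications, it is a weak guide.
- Routine or emergency status gives urgency, and ASA class gives general fitness. Neither gives a diagnosis.

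These are partial proxies.

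**How many patients could still be covered?** From Results: 2119 patients by January 2016. From the Abstract: 5000 expected. From Trial Duration and Schedule: January 2013 to December 2018, or 72 months, of which about 36 had passed.
- If the expected total is reached: 5000 − 2119 = 2881 still to come.
- If the pace to date simply continued (assumed): 2119 / 36 ≈ 59 per month, and 59 × 36 ≈ 2120 still to come.

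So about 2100 to 2900 patients, across all procedures, remained to be enrolled at that date. The share with a procedure other than cholecystectomy is not given, so the number who gain or lack an indication cannot be derived.

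**The case against.** Four points can be made for the plan.

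First, indications could mean the operations for which the technique is used, which type of surgery would capture. The article's own usage speaks against this: it lists indication separately from type of surgery and asks for it within cholecystectomy, where it can only mean the reason for that operation.

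Second, cholecystectomy dominates the cited literature, and bile duct injury is the article's leading example of a rare complication that needs large numbers. This may explain why the field was confined to it, and it limits the damage. It does not reconcile the field with an aim that covers all procedures.

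Third, age, sex, height, weight, ASA class, urgency and type of surgery are all collected, and the regressions are exploratory. This stands: case-mix adjustment is incomplete but possible, and no confirmatory test is at risk. A reader might infer that the strongest case-mix variable is missing, but the article gives nothing by which to rank these variables.

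Fourth, a reader might infer a second unmet aim from the Introduction: "This study focuses on external validity, clinical relevance, and the patient perspective". No patient-reported item is listed, and "The duration of the trial for each patient is limited to the hospital stay". Yet this is an undefined focus in the framing text. It is not part of the aim in Trial Objectives, and no planned analysis or conclusion promises a patient-reported result. Complications and length of stay also matter to patients. Adding pain or satisfaction scores would be debatable, since they would be unblinded and without a comparator, and the Discussion itself faults pain studies for lack of blinding. This supports a wording note and no more.

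**Conclusion.** The point holds as an inconsistency between Trial Objectives and Outcome Variables. One of the four elements of the aim cannot be met for any procedure other than cholecystectomy, and in those procedures the subgroup and exploratory regression analyses cannot take account of the reason for surgery.

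It should be put right, but it does not undermine the study. Mortality, morbidity and technical aspects can still be described for all procedures, and indications can be described for cholecystectomy. It would go too far to say that the aim as a whole is unanswered: indications are one element, and standing first in a sentence does not make them the main one. The number of patients affected is unknown, and any figure would rest on an assumed procedure mix.

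The conclusion assumes that the printed restriction reflects the database as built.

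**What to change.** Extend the indication field in the existing Internet database to every procedure, for patients enrolled from the change onward. Use it to describe each procedure group and as a case-mix factor in the procedure-specific analyses. The later this is done before December 2018, the fewer patients it reaches.

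If this is declined, restrict the aim in Trial Objectives to indications for cholecystectomy, which is a change of wording only.

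The cost of the first option is one more entry per patient. The indication will remain missing for patients already enrolled with other procedures, so reports should state from which date it is available. Back-entry should not be counted on: the article does not say that the centers hold a retrievable diagnosis code, and only 27 of the 106 registered centers were described as very active.

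As a separate wording note, the claimed focus on the patient perspective in the Abstract and Introduction should be removed, or qualified to say that no patient-reported outcome is listed.

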## Discussion

### Principle Considerations

Extensive literature exists on laparoscopic abdominal surgery. Conventional laparoscopic surgery requires a number of ports and a specimen extraction incision. Surgeons all over the world try to minimize abdominal wall trauma by using single-incision surgery. Single-incision surgery can use a single port system or a single-incision multiport approach [31-34]. Retrospective and randomized prospective studies could show the feasibility of this type of surgery without any increased risk to the patient. Of course, patients are usually selected and surgeons are very experienced. This limits the power of these studies. Some studies show advantages for single-incision surgery in postoperative pain, cosmetics, and patient satisfaction [35-39]. However, studies focused on pain were not blinded, which could lead to a relevant bias. Operative time was usually longer for the single-incision single port/multiport techniques [40]. Advantages of single-incision laparoscopic surgery, for example, reduced risk of hemorrhage or hernia, are intuitive at this time. The previous randomized prospective studies have too few patients to answer important questions in this area because of the low frequency of some relevant complications. For instance, it is still unclear if single-incision surgery leads to an increase in common bile duct injuries. To answer this question in a prospective randomized study is not easy or feasible, because there would be a need for thousands of patients to be included.

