### Conclusion

The endpoints of this study will allow a comprehensive evaluation of the surgical technique of single-incision abdominal laparoscopic surgery and its results. The results of this prospective trial will be compared with available evidence (ie, data from prospective randomized studies or reviews of single-incision surgery and classic multiple trocar techniques) in order to substantiate the current knowledge in this area.

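### Intraoperative bleeding counts a switch to multiple trocars, which only single-incision operations can have, so its rate is not like-for-like with multiple-trocar evidence

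*Protocol article*

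**What the plan says.** Under Outcome Variables, bleeding during surgery belongs to morbidity and is defined as "any bleeding during surgery that required conversion to an open approach or to an multiple trocar approach or required transfusion". There are three triggers, and any one is enough.

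The same section defines the later bleeding endpoint as "intraabdominal bleeding after surgery (requiring transfusion or surgery"; neither of its triggers depends on how the abdomen was entered. It also lists changes of access as assessment items of their own, outside morbidity: "conversion rate (conversion from single incision to an open approach), and need for additional trocars".

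Trial Design states that "SILAP is a prospective nonrandomized multicenter observational quality study with no intervention", so there is no concurrent control group. The Conclusion says that the results will be compared with available evidence, described as "data from prospective randomized studies or reviews of single-incision surgery and classic multiple trocar techniques".

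The Discussion (Principle Considerations) mentions haemorrhage once: "Advantages of single-incision laparoscopic surgery, for example, reduced risk of hemorrhage or hernia, are intuitive at this time". The safety question it names as open is a different one: "it is still unclear if single-incision surgery leads to an increase in common bile duct injuries".

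The article does not say that the three triggers will be reported separately, or that a narrower bleeding definition will be used for the external comparison.

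**The concern.** An operation already performed through multiple trocars cannot be converted to a multiple-trocar approach. One of the three ways of becoming a bleeding event is therefore open only to single-incision patients. Suppose the same bleed occurs under both techniques and is controlled laparoscopically without transfusion. In the registry it is a morbidity event if the surgeon had to change to multiple trocars to control it. Scored on the same definition, it is no event in a conventional laparoscopy.

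The endpoint thus mixes a safety outcome with a feasibility outcome that the study already assesses separately. Bleeding is one of the listed complications during surgery, so the mixture carries into any overall intraoperative morbidity rate. A reader who puts either rate beside multiple-trocar results could take a difference in definition for a difference in safety, and a real reduction in serious bleeding could be hidden.

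**Working it through.** **Is there a figure to reproduce?** No. The article gives no bleeding rate, power, significance level or margin, and states that a sample size calculation is not relevant. The check is a reading of the definition, followed by an illustration under assumed rates.

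**Step 1: which triggers can each technique meet?**

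| Trigger | Single incision | Multiple trocar |
|---|---|---|
| Conversion to open | yes | yes |
| Transfusion | yes | yes |
| Conversion to multiple trocars | yes | no |

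Two triggers are shared and one is not. For bleeding after surgery, both triggers are shared.

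**Step 2: size of the effect.** Let p be the rate of intraoperative bleeding with open conversion or transfusion, assumed equal under both techniques. Let t be the rate of bleeding that qualifies only through the switch to multiple trocars. Assume the comparator is scored on the two shared triggers. Then

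apparent ratio = (p + t) / p.

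Both p and t are assumptions.

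| p | t = 0.25% | t = 0.5% | t = 1% |
|---|---|---|---|
| 0.5% | 0.75/0.5 = 1.5 | 1.0/0.5 = 2.0 | 1.5/0.5 = 3.0 |
| 1% | 1.25/1 = 1.25 | 1.5/1 = 1.5 | 2/1 = 2.0 |
| 2% | 2.25/2 = 1.125 | 2.5/2 = 1.25 | 3/2 = 1.5 |

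In the 5000 patients expected in the Abstract, the trocar-only events would number 5000 × 0.0025 = 12.5, 5000 × 0.005 = 25, or 5000 × 0.01 = 50.

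**Step 3: can a true benefit be hidden?** Take a comparator rate of 1%, a single-incision rate of 0.5% on the shared triggers (true ratio 0.5) and t = 0.5%. The composite is 0.5% + 0.5% = 1.0%, an apparent ratio of 1.0. The halving disappears.

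**Step 4: effect of restricting the comparison.** Using only the shared triggers sets t = 0 in the formula. The ratio is then p/p = 1.0 when true bleeding is equal, for every p.

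**Step 5: can the triggers be separated in data already collected?** Only in part, as far as the article shows. A bleeding event with neither open conversion nor additional trocars must have qualified through transfusion. One with additional trocars and no open conversion may or may not also have needed transfusion. The article does not show whether the form records transfusion or links a change of access to bleeding as its reason.

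**The case against.** The strongest reply is that this is a descriptive registry of one technique. Its stated aim is to collect data in daily use, its analysis is frequencies plus exploratory regression, and no haemorrhage hypothesis or test is set. Bleeding severe enough to force the surgeon off the chosen access is a defensible severity threshold for centre quality reports. Part of the planned comparator is single-incision evidence, where the trigger is equally available. All of this stands, and it is why the composite should be kept for those uses. It does not cover the multiple-trocar part of the comparison, which the Conclusion also names.

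Three stronger readings are tempting, and the article does not support them.

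- A reader might infer that the study cannot tell whether haemorrhage differs. That goes too far. Two triggers are shared, bleeding after surgery is defined independently of access, and a composite rate below a comparator scored on the shared triggers would still be informative. Nor is haemorrhage set as a question to be answered. The remark about "reduced risk of hemorrhage or hernia, are intuitive at this time" is discussion background; paired with hernia, it may refer to the access site.
- A reader might infer that the bias always runs against single-incision surgery. That holds only against a comparator scored on open conversion or transfusion. A published study that counts any noted bleeding, or any bleeding needing an intervention, could differ in the opposite direction and offset or reverse the effect. The article does not say how its sources define bleeding.
- A reader might infer a large excess, such as two- to four-fold. A ratio of at least 2 requires trocar-only bleeds to be at least as frequent as all bleeds with open conversion or transfusion; a ratio of 4 requires three times as many. Nothing in the article supports either.

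The reply that the access items already solve the problem stands only partly. They may make the events separable, but the article does not say that they will be separated.

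**Conclusion.** The point holds as one of comparability. As defined, the intraoperative bleeding rate contains a component that multiple-trocar surgery cannot have, so it should not be set beside multiple-trocar evidence as if the two measured the same thing. The same applies to any intraoperative morbidity rate that includes it.

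The inflation equals t, against a comparator scored on the shared triggers. Its size is unknown. The illustrative range of about 1.1 to 3 rests on assumed values of p (0.5% to 2%) and t (0.25% to 1%) and on equal true bleeding. The net direction against any given source stays open until that source's definition is read. Comparison with single-incision evidence and the registry's own reports is not undermined by the trigger itself. The change is worth making because the definition is stated and the comparison is announced, while the remedy is small.

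**What to change.** - Record the trigger or triggers of each intraoperative bleeding event, and tabulate events as transfusion, open conversion, or multiple trocars only.
- For comparison with multiple-trocar evidence, use bleeding with transfusion or open conversion, and build any compared intraoperative morbidity rate on the same basis. State each source's bleeding definition next to its rate.
- Keep the full composite for annual centre reports and for comparison with single-incision evidence.
- Show bleeds that led only to multiple trocars beside the additional-trocar item, as a feasibility result.
- For patients already enrolled (2119 as of January 2016), split events from the existing conversion and additional-trocar fields as far as the form allows, and report how many cannot be classified. Against the expected 5000, 5000 − 2119 = 2881 patients remained at that date for prospective recording.

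The cost is one database sub-item, one extra table row and a possibly incomplete split for earlier patients. Clinical care is unaffected.
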